**Methods:**

A prospective, 3-year cohort study will be conducted. This study aims to recruit 6350 individuals across rural and urban settings of Chennai. A total of 11 sites have been selected for participation in the study. Data on sociodemographic characteristics; economic inequity; HEAL profile; depression, anxiety, and stress; well-being; sources of health information; perceived access to health care; health literacy; navigation of health literacy; and satisfaction with the health system will be gathered. This study would help to explore the determinants of social, economic, and health inequity across multiple sites. SAS (version 9.3; SAS Institute Inc) will be used for data analysis, and results will be reported as 95% CI and *P* values. This study’s findings will guide the design and development of a tailored, human-centered digital health intervention to enhance the health and well-being of Chennai’s population groups.

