### Study Design and Population

The HEAL cohort study is a prospective, 3-year cohort study with the aim to recruit 6350 individuals across rural and urban settings of Chennai, Tamil Nadu. The study sample will be recruited from Kannur; Pannur; Thirumenikuppam; Thodukadu; Kottaiyur; Nemili; Mannur; Kiloy; Ulundai; Narasamangalam; Karanai; Panimalar Medical College Hospital and Research Institute; Rural Training Health Centre Chennai; and Maligaipaddu village of Chennai, Tamil Nadu. Baseline evaluation will be performed at the time of recruitment of study participants. The study participants will be recruited through convenience sampling. This will serve as cross-sectional data to estimate the prevalence of determinants of social, economic, and health inequity.

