#### Economic Inequity

The wealth index is a division of households into 5 wealth quintiles to show the relationship between wealth, population, and health indicators [20].

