### Data Analysis

Descriptive analysis will be conducted to report the mean and SD of the continuous variables and frequency analysis of the categorical variables. A 1-tailed *t* test will be performed to compare means between the continuous variables and a categorical dependent variable while a chi-square analysis will be performed for the categorical variables. Multivariate regression analysis will be performed to determine the determinants of social, economic, and health inequity. All analysis will be performed using SAS (version 9.1; SAS Institute Inc), and reporting of the results will be done at 95% CI and *P*<.05.

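### The named t and chi-square tests ignore site: with 6350 people from 11 or 14 places, prevalence intervals and between-site comparisons can look more precise than they are

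*Protocol article*

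**What the plan says.** The Study Design and Population section of the Protocol article describes a "prospective, 3-year cohort study with the aim to recruit 6350 individuals across rural and urban settings". On sampling it says: "The study participants will be recruited through convenience sampling". The Abstract states: "A total of 11 sites have been selected for participation in the study". The Methods list starts "The study sample will be recruited from Kannur; Pannur; Thirumenikuppam; Thodukadu; Kottaiyur; Nemili; Mannur; Kiloy; Ulundai; Narasamangalam; Karanai" (11 names) and goes on to a hospital, a rural training health centre and one more village, 14 places in all. The baseline data are also to serve as a cross-sectional sample for prevalence estimates.

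The Data Analysis section sets a one-tailed t test for means, then: "while a chi-square analysis will be performed for the categorical variables. Multivariate regression analysis will be performed", the regression being the step that identifies determinants. Results are to be reported with 95% CIs and P<.05. No site effect, cluster adjustment or survey variance is mentioned.

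Three other places bear on the size of the problem:
- The Abstract says of the aim: "This study would help to explore the determinants of social, economic, and health inequity across multiple sites".
- The Economic Inequity section says: "The wealth index is a division of households into 5 wealth quintiles".
- The Study Intervention section says that the study location covers urban and rural areas of the selected sites. This does not settle whether urban/rural status is fixed for a whole site or varies within it.

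**The concern.** People from one village or one facility tend to resemble each other in diet, activity, access to care and income. With several hundred people per place, even a weak resemblance means that 6350 people carry much less information about between-place differences than 6350 independent people would. The t test and the ordinary chi-square test do not see this.

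Two kinds of result are exposed. The first is prevalence estimates read as applying to Chennai's rural and urban population groups rather than only to the listed places. The second is comparisons of groups that differ mainly by site. If each site is wholly urban or wholly rural, the urban-rural comparison is of this kind, and ordinary village-to-village differences could pass as an urban-rural effect. Objective 1 concerns determinants among rural and urban groups, so such comparisons are likely to be read closely.

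**Working it through.** **Inputs from the article.** N = 6350; 11 sites (Abstract) or 14 places (Study Design and Population); one-tailed t test, chi-square test, P<.05, 95% CI (Data Analysis). There is no ICC, design effect or sample-size calculation, so there is no figure of the plan's own to reproduce.

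**Assumptions.** Equal site sizes; ICC values from 0.001 to 0.05; and, for prevalence, inference beyond the listed places.

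**Step 1: people per site.** 6350/14 = 453.6; 6350/11 = 577.3.

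**Step 2: site-level factor or prevalence.** The design effect is DEFF = 1 + (m − 1) × ICC. At ICC 0.01:
- 14 places: 1 + 452.6 × 0.01 = 5.53, effective N = 1149.
- 11 sites: 1 + 576.3 × 0.01 = 6.76, effective N = 939.

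**Step 3: true error of a nominal 5% test.**
- Two-sided, 2 × [1 − Φ(1.96/√DEFF)]: 1.96/√5.53 = 0.83 gives 40%; 1.96/√6.76 = 0.75 gives 45%.
- One-sided, 1 − Φ(1.645/√DEFF): 24% and 26%.

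**Step 4: 95% half-width for a 50% prevalence.** 1.96 × √(0.25/6350) = 1.23 points under independence. Multiplied by √5.53 = 2.35 and √6.76 = 2.60, this becomes 2.9 and 3.2 points.

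Over a range of assumed ICCs (14 places to 11 sites):

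| ICC | DEFF | Two-sided error | One-sided error | Half-width, points |
|---|---|---|---|---|
| 0.001 | 1.45-1.58 | 10-12% | 9-10% | 1.5 |
| 0.005 | 3.3-3.9 | 28-32% | 18-20% | 2.2-2.4 |
| 0.01 | 5.5-6.8 | 40-45% | 24-26% | 2.9-3.2 |
| 0.02 | 10-12.5 | 54-58% | 30-32% | 3.9-4.4 |
| 0.05 | 24-30 | 69-72% | 37-38% | 6.0-6.7 |

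A simulation with 1500 runs per setting agrees at ICC 0.01: 43-45% two-sided and 26-27% one-sided.

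**Step 5: urban/rural varying within sites, unrelated to site.** Simulated error is about 5% (4-5%) even at ICC 0.05.

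**Step 6: wealth, which varies within sites.** DEFF = 1 + (m − 1) × ICC(outcome) × ICC(wealth).
- Outcome ICC 0.01, wealth ICC 0.02: DEFF 1.09-1.12, two-sided error 6%.
- Outcome ICC 0.01, wealth ICC 0.10: DEFF 1.45-1.58, 10-12% by formula and about 8% simulated with wealth split at the median.
- Outcome ICC 0.05, wealth ICC 0.10: 28-32% by formula, 19-23% simulated.

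With site as a fixed effect, the simulated error for such a within-site factor was 4-6%.

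**Step 7: households, only if several members enrol.** DEFF = 1 + (b − 1) × ICC(household). For an assumed 2 to 4 members and ICC 0.1 to 0.5, DEFF is 1.1-2.5. The error for a household-level factor is 6-22% two-sided or 6-15% one-sided.

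**The case against.** The best reply is that the article condenses a fuller plan and that determinants are to be identified by the regression, not by the bivariate tests. The regression is left open: its type, covariates, site terms and variance estimator are not given and may stand in an analysis plan that is not at hand. That part of the reply holds. A reader might infer that the regression also ignores site, but the text does not say so, and the charge is firm only for the t test and the ordinary chi-square test. Those are named and will be reported with P values and CIs, so the reply does not clear them.

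Three stronger readings are also tempting and go beyond the text:
- *Participants come from shared households.* The article records household size and defines wealth by household, but never says how many members of a household may enrol. It neither states nor excludes several.
- *Urban-rural comparisons will be falsely significant far more often than 5%.* This requires urban/rural status to be fixed by site, which the Study Intervention section leaves open.
- *Wealth comparisons are affected just as strongly.* Wealth varies within sites, and at an outcome ICC of 0.01 the inflation is modest.

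It is also fair to say that every magnitude rests on an assumed ICC, and that the Abstract calls the aim exploratory. That lowers the stakes of a single P value. It does not make an interval correct.

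**Conclusion.** The point holds in a conditional form. The named t and chi-square tests treat people grouped in 11 or 14 places as independent. Prevalence CIs and comparisons that differ mainly between sites can therefore have standard errors that are too small.

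On the ICC 0.01 assumption, which the article neither gives nor contradicts, the inflation for a purely site-level contrast is severe. It arises from the number of people per site and does not need a large ICC: at 0.001 the two-sided error already doubles to 10-12%. For a factor spread evenly within sites there is no material inflation. For wealth, about 6-12% two-sided at outcome ICC 0.01 is a reasonable range, and more needs stronger assumptions. Household clustering is a possibility to provide for, not an established defect.

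The intervention-control comparison is outside this point. The Study Intervention section reads as allocation of individual participants, and site clustering does not inflate such a comparison.

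**What to change.** State in the Data Analysis section that the prevalence, bivariate and regression analyses account for site:
- For determinants that vary within sites, include site as a fixed effect.
- For site-level contrasts and prevalence CIs, use a mixed model, or a Rao-Scott or other cluster-adjusted test, with small-sample degrees of freedom: number of sites minus number of site-level parameters. For one urban-rural contrast that is 11 − 2 = 9 or 14 − 2 = 12. An uncorrected robust variance with 11 to 14 clusters would itself be too liberal.
- Say whether urban/rural status is assigned to the site or to the participant, since this decides which of the two applies.
- Put a site code and a household ID on the paper form, so that household clustering can be handled if it occurs.

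The cost is a few sentences, two form fields, a little more analysis work in SAS (already the planned software), and wider CIs. The Results section reports that, as of December 2024, baseline recruitment had not begun. The codes are cheap to add now and may be impossible to recover later.

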### Projected Timelines and Milestones

A detailed research plan and scheduled timeline of the tasks involved in the study are presented in Table 1.

**Table 1 table1:** Scheduled timeline of the tasks in the HEAL^a^ study.

Variables	Month 1	Months 2-5	Months 6-7	Months 8-10	Months 11-18	Months 14-30	Months 31-33	Months 34-36
Stakeholder meeting	✓							
Baseline data collection		✓						
Design and development of human-centered intervention			✓					
Heuristic evaluation			✓					
Usability of the proposed system				✓				
Refine the proposed SMAART^b^ informatics self-management intervention				✓				
Final deployment of the proposed SMAART informatics self-management intervention tool				✓				
Study recruitment (baseline data)					✓			
Follow-up data collection					✓	✓		
Statistical analysis					✓	✓	✓	
Report writing and paper preparation							✓	✓

^a^HEAL: Healthy Eating Active Living.

^b^SMAART: Sustainable, Multi-Sector, Accessible, Affordable, Reimbursable, Tailored.

The study is in accordance with the STROBE (Strengthening the Reporting of Observational Studies in Epidemiology) guideline for case-control studies (Multimedia Appendix 1) [30].

## Results

As of December 2024, the literature review for the development of the intervention has been completed. Recruitment for the baseline data collection is scheduled to begin in the upcoming months, followed by the development of HEAL intervention.

The findings of the study will be disseminated through peer-reviewed publications and national and international conference presentations.

## Discussion

### Expected Findings

In order to reduce the health inequity in India, it is imperative to have the requisite knowledge base. This study would help to fill the research and knowledge gap by identifying key areas that need to be addressed to improve the health status of the population. The baseline data will enable us to find the socioeconomic inequity faced by the participants, their health literacy, and their awareness regarding their health status and health care. These findings would also help to design and develop tailored population health interventions to enhance the healthy eating and active living of the population groups.

Health inequities have existed throughout time, as resonated by the concept of inverse care law (1971), which highlighted how good medical care is inversely related to people’s needs in low- and middle-income countries [31]. Similarly, Cookson et al [32] recently proposed the law of disproportionate care (2021) where they argue that in high-income countries, socially disadvantaged groups receive more care but of worse quality to meet their health care needs. The available studies also reinstate the need to address health inequities by collecting and analyzing the relevant health equity data [33]. This study would therefore help in filling the requisite knowledge gaps by identifying the key determinants of health inequity. It would also help in contributing to the advancement of evidence-based strategic decisions on health inequity. The findings from this research project would also help in designing, developing, and implementing data-driven, evidence-based, and human-centered interventions to enhance the healthy eating and active living of the population groups.

### Limitations

This study’s limitations include that it is confined to one geographic region, and implementing it in diverse geographic and population settings would help to better understand and compare the impact of the HEAL intervention.

### Conclusions

The HEAL intervention offers a model to enhance healthy eating and active living for the individuals participating in the study through the SMAART framework. The findings from the study will contribute to the understanding of the role of digital health interventions to enhance healthy eating and active living of the population groups, which will help in understanding and addressing determinants of health equity in the population.

## Appendix

Multimedia Appendix 1 STROBE (Strengthening the Reporting of Observational Studies in Epidemiology) checklist.

## Abbreviations

DASS: Depression Anxiety, and Stress Scale
HEAL: Healthy Eating Active Living
SMAART: Sustainable, Multi-Sector, Accessible, Affordable, Reimbursable, Tailored
STROBE: Strengthening the Reporting of Observational Studies in Epidemiology
WHO: World Health Organization
